##### Secondary estimands

(1) Assessment of tolerability and acceptability of treatment versus placebo through the Functional Assessment of Cancer Therapy measured using health-related quality of life and patient perspective questionnaires.

Population: As per primary estimand.

Treatment: As per primary estimand.

Variable: Scores arising from health-related quality of life EQ-5D-5L (EuroQol-5 descriptive-5 level) and EORTC patient perspective (EORTC_QLQ-C30) questionnaires.

Population-level summary: The model-produced estimate for the treatment×time interaction effect at day 28, plus at follow-up time points days 100, day 200 and day 365.

Intercurrent events: Death, AE/SAEs, rescue therapy outside of antibiotic use, loss to follow-up/withdrawal.

Strategy to handle intercurrent events: Treatment policy as primary estimand

(2) Assessment of changes in inverse Simpson’s index and other measures of gut microbiome diversity across all time points assessed, including alpha diversity and richness (ie, as measured via Chao-1, Shannon, Faith’s PD) and beta-diversity (Aitchinson’s distance) as well as changes in gut microbiome taxonomic composition.

Population: As per primary estimand.

Variable(s): As per primary, plus Chao-1, Shannon, Faith’s PD, Aitchinson’s distance and taxonomic composition.

Population-level summary: The model-produced estimate for the treatment×time interaction effect at days 7 and 14. Interaction effect for follow-up visit time points day 100, 200 and 365 will also be assessed.

Intercurrent events: Death, AE/SAEs, rescue therapy outside of antibiotic use.

Strategy to handle intercurrent events: Treatment policy as primary estimand.

(3) Clinical endpoints including markers of general health, infective/microbiological and haematological outcomes across all time points measured, including admission to intensive care unit, survival, non-relapse mortality, relapse incidence; occurrence and severity of GvHD, overall and GvHD-free relapse-free survival and quality of life.

Population: As per primary estimand.

Variable(s): Overall and GvHD-free relapse-free survival.

Population-level summary: Log-rank test statistic, HR (with 95% CI).

Intercurrent events: Death unrelated to patient comorbidity (relapse-free survival only), death related to patient comorbidity (relapse-free survival only), loss to follow-up/patient withdrawal, AE/SAEs, rescue therapy outside of antibiotic use.

Strategy to handle intercurrent events: Death unrelated to patient comorbidity (relapse-free survival only) will be censored at the recorded time of death as part of a hypothetical strategy. Where death is potentially related, a composite strategy is to be considered where time of death will be taken as time of relapse. Loss to follow-up/patient withdrawal will be censored at time of last contact as part of a hypothetical strategy. Treatment policy will be used on use of rescue therapy or under any AE/SAE which does not result in the withdrawal of the patient.

Estimands for additional variables covered in secondary outcome #3 will be provided within the SAP. These include markers of general health (intensive treatment unit admission, severity of mucositis, occurrence of severe acute kidney injury (AKI), occurrence of severe liver dysfunction, use of oarenteral nutrition), infective haematological outcomes (fever occurrence, fever CTCAE grade, infection, multidrug-resistant bacterial colonisation (MDROs), antibiotic use), neutrophil and platelet engraftment data, recovery of T-cell chimerism, haematological outcomes (non-relapsed mortality, occurrence GvHD, severity of GvHD).

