**Methods and analysis:**

50 adult patients receiving allogeneic HCT will be recruited into this phase IIa trial and randomised 1:1 to receive capsulised IMT or matched placebo shortly prior to initiation of HCT conditioning and followed for up to 12 months. The primary outcome will be to assess the increase in alpha diversity between pre-IMT and that measured at ~42 days after IMT administration (day +28 of HCT), comparing the difference between patients receiving IMT compared with placebo. Secondary outcomes will include tolerability, the dynamics of gut microbiome diversity metrics and taxonomy over all time points assessed, as well as clinical outcomes (including burden of invasive infections, days of fever, admission to intensive care, development of graft-vs-host disease and mortality).

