### Analysis of secondary estimands

The complete-case analysis will follow the same model as defined in analysis of primary estimand (using only patients attending all visits as per estimand). Mixed-effect models incorporating a per-patient random effect alongside effects for time of assessment, and an interaction term of time-by-arm assessing changes in alpha diversity(inverse Simpson’s index, Chao-1, Shannon index, Faith’s PD) and β-diversity will provide treatment effects and 80% CIs at response assessments 1–5 and follow-up assessments 1–3 (see figure 1). Similar approaches will be used to assess changes in gut microbiome taxonomic composition based on shallow shotgun sequencing.

Overall survival (time from randomisation to death/date last seen alive) will be analysed using Kaplan-Meier methods and log-rank testing using the same stratification variables as per primary analysis model defined in analysis of primary estimand. Additional survival analysis will include non-relapse mortality and GvHD-free relapse-free survival.

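### GvHD-free relapse-free survival censors deaths judged unrelated to comorbidity, which removes part of non-relapse mortality from an endpoint in which death is a failure

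*Protocol article*

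**What the plan says.** All of this is in the protocol article. Item (3) under Secondary estimands names two time-to-event variables: "Variable(s): Overall and GvHD-free relapse-free survival". Its list of intercurrent events divides deaths by their relation to comorbidity: "Death unrelated to patient comorbidity (relapse-free survival only), death related to patient comorbidity (relapse-free survival only". No plain relapse-free survival variable is listed, so the restriction in brackets can only refer to GRFS.

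Two handling rules follow. For unrelated deaths: "Death unrelated to patient comorbidity (relapse-free survival only) will be censored at the recorded time of death as part of a hypothetical strategy". For the others: "Where death is potentially related, a composite strategy is to be considered where time of death will be taken as time of relapse". The summary measure is given as "Population-level summary: Log-rank test statistic, HR (with 95% CI".

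Under Analysis of secondary estimands, overall survival counts every death: "Overall survival (time from randomisation to death/date last seen alive) will be analysed using Kaplan-Meier methods". The same section adds: "Additional survival analysis will include non-relapse mortality and GvHD-free relapse-free survival". The abstract says that patients are "followed for up to 12 months".

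Item (3) leaves the estimands of its further variables to the SAP. GRFS is not among those; its rule is fixed in the article.

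**The concern.** GRFS is meant to describe being alive, free of GvHD and free of relapse. Death without either is a failure. The article accepts this for potentially related deaths, since it would turn them into events, and then exempts the rest.

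Censoring at death says that the patient would have continued with the same hazard of GvHD and relapse as those still under follow-up. A patient who has died has no such future, and after a transplant the patients who die are unlikely to resemble the survivors. The censoring is therefore informative, and the resulting curve describes a population in which these deaths do not happen.

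The dividing line adds a second problem. It runs along comorbidity, not along disease or transplant, and the article defines neither the term nor how relatedness is judged. Read literally, a fatal infection in a patient with no relevant comorbidity could be censored. The Introduction links low diversity to transplant-related death and cites fewer bloodstream infections and better survival after IMT, so some of the deaths at issue may be ones that IMT is hoped to prevent. The Discussion presents the trial as a basis for phase III work. A GRFS estimate with some deaths removed would be a poor input to that, and would not be comparable with one that counts every death.

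**Working it through.** The article states no figure for GRFS, so there is none to reproduce. The sizes below rest on assumed rates and show direction and scale only.

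**Inputs (assumed).** Net one-year risks without IMT: relapse 25%, GvHD 25%, non-relapse death 20%; constant cause-specific hazards over one year, h = −ln(1 − p).

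- Relapse: h_r = −ln 0.75 = 0.288
- GvHD: h_g = −ln 0.75 = 0.288
- Non-relapse death: h_n = −ln 0.80 = 0.223
- Sum = 0.799

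**Level of GRFS.** With a share f of the non-relapse deaths censored, the estimate is exp[−(h_r + h_g + (1 − f)h_n)].

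| Share censored | Calculation | One-year GRFS |
|---|---|---|
| 0 | exp(−0.799) | 45% |
| 0.5 | exp(−0.687) | 50% |
| 1 | exp(−0.575) | 56% |

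The share of first events that are deaths is 0.223/0.799 = 0.28. At these rates in both arms, 50 patients have 50 × 0.55 = 27.5 GRFS events, of which about 7.7 are deaths. Those 7.7 are the most that the rule could remove.

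**Other inputs.** Now set the one-year probability of GvHD or relapse as first event at 30% to 50%, of death as first event at 5% to 20%, and the censored share at 25% to 100%. GRFS is overstated by about 1 to 16 points. The top of the range has 30% and 20% with all deaths censored: the total hazard is −ln 0.50 = 0.693, the GvHD/relapse part is 0.693 × 0.3/0.5 = 0.416, and exp(−0.416) = 66% against 50%.

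**Hazard ratio, IMT to placebo, on the first set of inputs.**

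| IMT effect | All deaths counted | Half censored | All censored |
|---|---|---|---|
| Halves non-relapse death only | (0.575 + 0.112)/0.799 = 0.86 | (0.575 + 0.056)/0.687 = 0.92 | 1.00 |
| Doubles non-relapse death only | (0.575 + 0.446)/0.799 = 1.28 | (0.575 + 0.223)/0.687 = 1.16 | 1.00 |
| Halves GvHD only | (0.288 + 0.144 + 0.223)/0.799 = 0.82 | (0.288 + 0.144 + 0.112)/0.687 = 0.79 | 0.432/0.575 = 0.75 |

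The ratio moves toward the effect on GvHD and relapse alone. A benefit or a harm that acts through death is diluted; a benefit that acts through GvHD looks larger than it is on the full endpoint.

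**Limit of the calculation.** It treats the three hazards as independent, so it shows only the effect of leaving deaths out of the event definition. Dependence between death and the other events would make the hypothetical estimate harder still to interpret, by an amount that these documents do not allow one to compute.

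**The case against.** Much can be said on the other side.

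- **Only part of non-relapse mortality is lost.** A reader might infer that the rule strips out all of it. The text does not say so: potentially related deaths, possibly a wide class, would stay as events, and nothing shown places infection or toxicity deaths as a group in the censored class. This stands, and the all-censored figures are an upper limit.
- **GvHD deaths are mostly untouched.** GRFS is time to first event, so a patient who dies of GvHD has normally failed already. This stands; only deaths without prior GvHD or relapse matter.
- **The hazard ratio is not always pulled toward 1.** The GvHD row of the table shows the opposite. This stands; the direction depends on where IMT acts.
- **Taking time of death as time of relapse is harmless for the estimate.** It gives the same event at the same date as counting the death directly. This stands; the fault there is labelling, and the fact that the rule is only to be considered.
- **Non-relapse mortality.** A reader might infer from its place beside the overall survival analysis that Kaplan-Meier will be used for it, with relapse censored. The article names Kaplan-Meier only for overall survival and leaves the non-relapse mortality estimand to the SAP, so no fault is shown.
- **Precision is low.** With 27.5 events, SE(log HR) is about 2/√27.5 = 0.38, and the 95% interval around 0.86 runs from about 0.41 to 1.82. A shift from 0.86 to 0.92 would change no conclusion in this trial. This stands, but imprecision is no reason to estimate the wrong quantity.

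None of this answers the core point. Some deaths are censored in a survival endpoint, by a stated rule, on a judgement that the article does not define.

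**Conclusion.** The rule is wrong as written. It removes from GRFS those deaths without prior GvHD or relapse that are judged unrelated to comorbidity, and it leaves the counting of the remaining deaths undecided. On the assumed rates GRFS is overstated by about 5 points if half of the non-relapse deaths are censored and 11 if all are, and by about 1 to 16 points over the wider range. The actual share is unknown, because the article supplies neither event rates nor a rule for relatedness.

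The consequence is confined to one secondary endpoint. Overall survival keeps every death, non-relapse mortality is to be analysed separately, and the primary outcome and sample size concern alpha diversity. A reader might infer that deaths would be hidden from the trial report or that the main result is at risk; the document supports neither. The point should be fixed, but the trial's main conclusion does not hang on it.

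**What to change.** In item (3) of Secondary estimands, and in the SAP:

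1. Define GRFS as time to the first of GvHD as defined for this endpoint, relapse, or death from any cause, with death an event at its own date.
2. Delete the censoring of deaths unrelated to comorbidity, and replace the provisional rule for related deaths with the same all-cause rule. Deaths are then recorded as deaths and not as relapses.
3. If an analysis that sets some deaths aside is wanted, make it supplementary, give it its own name, and treat death as a competing event, for example as the cumulative incidence of GvHD or relapse. A breakdown of deaths by relation to comorbidity can be a descriptive table.

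The cost is a change of wording. No new data are needed, and the adjudication of relatedness is no longer required for the endpoint.

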### Analysis of primary estimand

The primary outcome of between-arm difference in alpha diversity change from baseline at day 28 (±3 days) will be analysed using a mixed-effects model, with change in alpha diversity from baseline as an outcome, with treatment arm, time, treatment-by-time interactions and stratification variables used in randomisation included as fixed effects and also a per-patient intercept included as a random effect. The subsequent model estimate for the treatment-by-time interaction term at day 28 will be the effect of interest as per primary estimand.

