## Methods and analysis

### Design and objectives

The Microbiota Transplant Prior to Allogeneic Stem Cell Transplant (MAST) study is a multicentre, randomised, phase IIa double-blind placebo-controlled trial. The major objective of this trial is to determine the ability of capsulised IMT given prior to allogeneic HCT to increase and maintain stool microbiota diversity after HCT from baseline. Secondary objectives include determination of clinical tolerability, effects of capsule IMT on clinical outcomes and to explore microbiome and immune dynamics related to IMT use. The primary outcome is the change in alpha diversity (measured as inverse Simpson’s index) after IMT administration measured immediately prior to IMT (at 14±3 days prior to HCT) and 28±3 days after HCT, comparing the change between patients receiving capsulised IMT versus placebo. The study is sponsored by Imperial College London. This is an investigator-led study; while funding for the study was only awarded after peer review, the funder, sponsor and industrial partner have had no direct role in any aspect of study design (although the funder arranged external peer review as part of the process to the award of funding, which did impact on study design). We have used the Standard Protocol Items: Recommendations for Interventional Trials (SPIRIT) checklist in writing this report.^17^

The study start date was April 2024, with primary completion estimated as August 2026 and study completion estimated as March 2027.

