### Interventions

#### Allocation

50 adult patients will be allocated 1:1 between two groups:

Capsulised IMT—as a single oral dose of 10 capsules of EBX-102-02. EBX-102-02 is encased within an intrinsically enteric-resistant capsule containing pooled, dried, full-spectrum microbial ecosystems obtained from rigorously screened donors. EBX-102-02 is characterised by the absence of pathogens, a minimum viable count of anaerobic micro-organisms and the presence of preidentified genera (such as *Faecalibacterium*), all measured by proprietary nucleic acid-based assays and other technologies. EBX-102-02 will be administered within 2 weeks of the initial study screening visit. Given the immunosuppressed nature of the recipients, out of an abundance of caution, EBX-102-02 will be prepared from CMV-negative donors, as per suggestions from current guidelines.^9^Matched capsulised placebo—containing microcrystalline cellulose and magnesium stearate; administered at the same point as capsulised IMT.

Treatment with either IMT or placebo will take place at 14 (±2) days prior to haematopoietic cell infusion in a hospital setting. Both IMT and placebo will be stored in a refrigerator (at 2°C–8°C) until administration, with temperature monitoring of the investigational medicinal product prior to administration. Study participants will be nil by mouth for at least 30 min prior to—and 1 hour after—each course of IMT/placebo capsule administration. They will be asked to take each capsule with sips of water and will be monitored for at least 15 min after capsule administration for complications (eg, nausea).

Randomisation will be performed centrally by the Imperial College Trials Unit (ICTU)—Cancer using OpenClinica electronic data capture system. The system applies stratified randomisation to reduce relevant imbalances and increase statistical power, randomisation will be stratified by disease history (either (1) patients known to have intestinal colonisation or bloodborne infection with MDROs during previous therapy or (2) patients without this history) to ensure there is a balanced distribution across treatment arms. To reduce predictability in the randomisation sequence, blocks of multiple sizes have been used during sequence generation.

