### Statistical considerations

#### Sample size and powering

Currently published data on alpha diversity change in patients undergoing HCT and/or IMT span different study types, vary in quality/granularity, and use different alpha diversity indices. The evidence available suggests larger decreases in alpha diversity at approximately 1-month post-HCT compared with baseline in patients who do not receive IMT relative to those that do.^2 6 8 18 19^ Fitting a mixed-effects model (with fixed effects for arm, time (day), their corresponding interaction and a random per-patient intercept effect) with quadratic splines at 5 df (3 internal knots) to longitudinal change in alpha diversity data (measured with inverse Simpson’s index) from baseline,^2^ IMT patients had an expected change in baseline alpha diversity at day 28 post-HCT 3.46 (pooled SE=2.19) units more than placebo (IMT mean change=−4.70, SE=1.44, n=14; placebo mean change=−8.16, SE=1.66, n=11). We have used these results on IMT post-HCT to design our study of IMT pre-HCT versus placebo.

Our null hypothesis is there is no difference between the change in days 28±3 days alpha diversity (inverse Simpson’s) post-HCT from baseline in patients receiving pre-HCT IMT compared with patients receiving placebo capsules (ie, the difference in between-arm changes from baseline is zero). Using a two-sample t-test to compare IMT-arm change to placebo-arm change with two-sided alpha controlled at 20%,^20 21^ we need 46 patients randomised 1:1 between IMT and placebo (23 per arm) to have ≥80% power to detect a between-arm difference of 3.46 units (with pooled SD of 5.45 estimated at day 28 post-HCT from mixed-effects model). To account for dropouts at a rate of up to 8% across both arms, we will recruit 50 patients in total. Modelling and sample size calculations have been performed using R V.3.6.1.

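### The primary model for change in inverse Simpson omits the baseline value already collected, giving up precision and leaving the day-28 contrast sensitive to chance baseline imbalance

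*Protocol article*

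**What the plan says.** Under Analysis of primary estimand, the protocol article specifies a mixed-effects model "with change in alpha diversity from baseline as an outcome, with treatment arm, time, treatment-by-time interactions and stratification variables used in randomisation" as fixed effects, and "also a per-patient intercept included as a random effect". On the quantity to be reported it says: "The subsequent model estimate for the treatment-by-time interaction term at day 28 will be the effect of interest as per primary estimand".

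The baseline value is available. Design and objectives defines the primary outcome as a change in diversity "measured immediately prior to IMT (at 14±3 days prior to HCT) and 28±3 days after HCT". Under Allocation, "randomisation will be stratified by disease history", which there means known MDRO colonisation or bloodborne infection, yes or no. Baseline diversity is not a stratification factor.

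Sample size and powering also works with unadjusted change: the planning model has arm, time, their interaction and a random intercept, and the size comes from a two-sample t-test on change. No section adds baseline inverse Simpson to the primary model. The Discussion mentions baseline diversity as a possible predictor, but only for an exploratory responder analysis within the treatment arm.

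**The concern.** A change score fixes the slope of day 28 on baseline at 1. Chemotherapy conditioning, often antibiotics, and the transplant itself lie between the two samples, and the Introduction describes marked loss of diversity over this process, so there is reason to doubt a slope of 1. If the slope is below 1, patients with a high baseline tend to show larger falls, and the arm that happens to start higher looks worse at day 28. With about 23 patients per arm such imbalance will occur by chance, and stratifying on MDRO history does not directly prevent it.

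What is at stake is precision and the reading of the single result, not validity. Baseline adjustment targets the same day-28 between-arm difference, usually with a smaller standard error, from a measurement that the trial makes anyway.

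**Working it through.** **Inputs from the article (Sample size and powering).** Difference 3.46; SD of change 5.45; two-sided alpha 0.20; 23 per arm; dropout 8%. The external data behind them: "IMT mean change=−4.70, SE=1.44, n=14; placebo mean change=−8.16, SE=1.66, n=11".

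**The plan's own figures.**
- SDs from the quoted standard errors: 1.44 × √14 = 5.39 and 1.66 × √11 = 5.51; pooled 5.44, in line with 5.45.
- Standard error of the difference at 23 per arm: 5.45 × √(2/23) = 1.61.
- Power from the noncentral t: 0.803 at 23 per arm, 0.790 at 22.
- 46 / 0.92 = 50.

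The stated 23, 46 and 50 all reproduce.

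**Effect of adding baseline.** Let r be the correlation of baseline with day 28 and s the SD at each time. Neither is in the article. Assume equal variances at the two times.
- Variance of change: 2s²(1 − r).
- Residual variance after adjustment: s²(1 − r²).
- Ratio: (1 + r)/2, so residual SD = 5.45 × √((1 + r)/2).
- Implied s = 5.45 / √(2(1 − r)).
- If the arms differ at baseline by one standard error, s√(2/23), the unadjusted estimate moves by (r − 1) × s√(2/23).

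Power uses the noncentral t with one further degree of freedom lost.

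| r | Residual SD | SE | Power | Shift per 1 SE of baseline imbalance |
|---|---|---|---|---|
| unadjusted | 5.45 | 1.61 | 0.80 | – |
| 0.3 | 4.39 | 1.30 | 0.91 | −0.95 |
| 0.5 | 4.72 | 1.39 | 0.88 | −0.80 |
| 0.7 | 5.02 | 1.48 | 0.85 | −0.62 |
| 0.9 | 5.31 | 1.57 | 0.82 | −0.36 |

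The last column is a movement of the unadjusted estimate. At r=0.5 it is 0.80/3.46 = 23% of the target difference.

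**Unequal variances.** Let k be the day-28 SD divided by the baseline SD; the slope of day 28 on baseline is then rk. With k=0.75, adjusted power runs from 0.98 (r=0.1) to 0.94 (r=0.7). With k=1.5 and r=0.7 the slope is 1.05 and power is 0.803, so there is no gain.

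**Does the random intercept do the job?** No. It models the correlation among a patient's change scores. In a simulation of the mixed model (23 per arm, three post-baseline visits, 300 runs per value of r), the unadjusted day-28 contrast correlated −0.64, −0.54 and −0.32 with baseline imbalance at r = 0.2, 0.5 and 0.8, and about 0 once baseline was in the model. The empirical SE fell from 1.63 to 1.26, from 1.67 to 1.42 and from 1.66 to 1.60.

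**Which quantity is reported matters.** Write Y0 for baseline, Yref for a post-baseline reference visit and Y28 for day 28. An interaction coefficient against that reference visit compares the arms on (Y28 − Y0) − (Yref − Y0) = Y28 − Yref. In complete, balanced data baseline cancels, so a baseline main effect alone changes little. The between-arm contrast at day 28 compares the arms on Y28 − Y0, where baseline does not cancel. The power figures above concern this second quantity, which is also what the sample size is built on.

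**The case against.** The strongest reply is that nothing here is wrong. Randomised change scores give an unbiased comparison and a valid test, planning and analysis both use unadjusted change, and the power target is met. Chance imbalance is variation that the standard error already covers. All of this stands. A reader might infer that the primary analysis is biased, invalid or underpowered; the documents support none of these. The sensitivity to imbalance is conditional on the imbalance that happens to occur.

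A second reply is that the size of the gain is not in the documents. This also stands. Both r and the equal-variance assumption are supplied from outside, and the power figures are for a single-visit adjusted comparison. In the mixed-model simulation at r=0.8 the gain was small.

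A reader might also argue that change must be strongly tied to baseline because inverse Simpson cannot be below 1: a mean fall of 8.16 needs a mean baseline of at least 1 + 8.16 = 9.16. The floor limits how far a patient can fall but does not show how strong the relation is. Under the equal-variance assumption the correlation of change with baseline is −√((1 − r)/2), which is −0.59 at r=0.3 but only −0.22 at r=0.9. Moreover, 8.16 is a model estimate from 11 external placebo patients in data on microbiota transplant given after HCT. It is not a fall that this trial plans for.

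Finally, the statistical analysis plan is not shown and may add baseline. That limits how certain one can be about the final model. It does not remove the point, because the article states the covariate list explicitly.

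**Conclusion.** The point holds as one of efficiency and robustness, worth acting on but not a fault in validity. As stated, the primary model leaves out a covariate that is already collected. Assuming equal variances and an SD of change of 5.45 at 23 per arm, adjustment would raise power for the day-28 contrast from 80% to between 82% (r=0.9) and 91% (r=0.3). The gain is larger if diversity varies less at day 28 than at baseline, and absent if the slope of day 28 on baseline is near 1. The article does not allow a choice within that range.

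**What to change.** In the statistical analysis plan, before unblinding:

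- Add baseline inverse Simpson and baseline-by-visit as fixed effects in the primary mixed model, and carry this into the complete-case analysis, which uses the same model.
- State that the reported effect is the model-based between-arm contrast at day 28, not an interaction coefficient against a post-baseline reference visit.
- Treat the other alpha-diversity indices (Chao-1, Shannon, Faith's PD) and the quality-of-life scores in the same way, each with its own baseline. Do not do so for a distance measured from the patient's own baseline sample, which has no baseline value to adjust for.
- Keep 46 evaluable and 50 recruited.

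The cost is a short amendment to the model text and a few degrees of freedom, more if every response and follow-up visit is modelled with its own baseline slope. No new data are needed. Added after unblinding, the adjustment would be post hoc.
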